## Abstract

**Background:**

The Wellness Together Canada (WTC) portal is a digital mental health intervention that was developed in response to an unprecedented rise in mental health and substance use concerns due to the COVID-19 pandemic, with funding from the Government of Canada. It is a mental health and substance use website to support people across Canada providing digital interventions and services at no cost. Two million people have visited the WTC portal over the course of 1 year since launching; however, rigorous evaluation of this potential solution to access to mental health care during and after the COVID-19 pandemic is urgently required.

**Objective:**

This study aims to better understand the effectiveness of the existing digital interventions in improving population mental health in Canada.

**Methods:**

The Let’s Act on Mental Health study is designed as a longitudinal fully remote, equally randomized (1:1), double-blind, alternative intervention–controlled, parallel-group randomized controlled trial to be conducted between October 2023 and April 2024 with a prospective follow-up study period of 26 weeks. This trial will evaluate whether a digital intervention such as the WTC improves population mental health trajectories over time.

**Results:**

The study was approved by the research ethics board of CAMH (Centre for Addiction and Mental Health, Toronto, Ontario, Canada). It is ongoing and participant recruitment is underway. As of August 2023, a total of 453 participants in the age group of 18-72 years have participated, of whom 70% (n=359) are female.

**Conclusions:**

This initiative provides a unique opportunity to match people’s specific unmet mental health and substance use needs to evidence-based digital interventions.

## Introduction

Mental health problems are the leading cause of global disability affecting worldwide populations including Canadians. The Bell Let’s Talk campaign promotes mental health awareness by engaging Canadians in encouraging people to speak up about mental health. Yet, many Canadians lack access to mental health care services, with equity in access being a key concern for specific groups (eg, gender, race and ethnicity, socioeconomic status, geographic isolation, and immigration status). As a result of the COVID-19 pandemic and preventive measures such as social distancing, an “echo pandemic” of declining mental health in the Canadian population has emerged [1]. The COVID-19 pandemic is exacerbating mental health challenges and widening service gaps, especially among those in marginalized groups and those with preexisting mental health issues [2,3]. Research on mental health during the pandemic has found that 40% of Canadians stated that their mental health has declined due to the COVID-19 pandemic, and 48% of individuals felt anxious or worried [4,5]. Even prior to the pandemic, the burden of mental illness was widespread in the population. Worldwide, an estimated 264 million people are affected by depression alone [6]. Mood and anxiety disorders are the most prevalent mental health issues in Canada, occurring among 11.6% of Canadian adults [7]. Our mental health care system is overwhelmed and too underfunded to address the pervasiveness of mental health challenges [8]. At the same time, many people are reluctant to maintain or improve their mental health, with a stigma-based perception that mental health is only an issue for people with a diagnosed mental disorder, rather than being a concern for everyone [9]. The experience of the COVID-19 pandemic demonstrates that it is critical to provide tools to all Canadians, which will improve mental health and provide self-assessment and self-help aids at the population level [10].

The digital intervention for mental health, the Wellness Together Canada (WTC) portal [11], was developed in response to an unprecedented rise in mental health and substance use concerns due to the COVID-19 pandemic, with funding from the Government of Canada. It is a mental health and substance use website to support people across Canada, providing digital interventions and services at no cost. It partners with other digital interventions to be the home portal for access to digital interventions from 1:1 support, peer groups, and self-help tools. WTC is a one-stop, web-based portal, available nationally, which provides all people in Canada with 24/7 free and confidential access to a web-based network of information and psychosocial support services, which comprise triage and self-monitoring tools, mental health promotion information, self-guided apps, coached and peer support programs, mental health counseling, and crisis intervention. Services are readily accessible, available in French and English, and are made available through a variety of digital media (eg, computer and phone) and web-based services (eg, voice, text, web-based chat, and responsive web design). The portal is stigma-free and recovery-oriented, providing a wide range of intervention options, and follows a continuous improvement process based on stakeholder engagement, program data, and user feedback. Two million people have visited the WTC portal over the course of 1 year since launching; however, rigorous evaluation of this potential solution to access to mental health care during and after the COVID-19 pandemic is urgently required.

This initiative provides a unique opportunity to match people’s specific unmet mental health and substance use needs to evidence-based digital interventions. Canadians will have a tool that provides valuable information, self-assessment on mental health, access to personalized digital interventions, and an avenue for everyone to participate in better understanding and improving mental health in Canada.

This study aims to evaluate the effectiveness and cost-effectiveness of the WTC portal by conducting a randomized controlled trial. The control group will be referred to the usual care tools available on the CAMH (Centre for Addiction and Mental Health) website. CAMH provides a range of self-care interventions, particularly different mental health programs and resources such as “Game Changers: Self-care information,” which is a hub of resources to help start a conversation about health, including a self-help booklet series, a relaxation guide, and free web-based education with a personalized dashboard, which provides an opportunity for the client to self-monitor (symptoms or physiological processes), build awareness, and improve self-efficacy and visualization. Usual care tools such as digital interventions have a self-care and self-help component. Many studies have shown positive outcomes deemed acceptable and feasible with >95% completion rates and a high degree of participation with self-care interventions; some offer significant early benefits of tailored self-care programs [12,13]. A meta-analysis indicates that these interventions can be effective and potentially be future home-based interventions, especially in mental health care such as digital interventions; hence, it has been chosen as a control intervention in this study.

## Methods

### Trial Design

The Let’s Act on Mental Health study is a longitudinal, fully remote, equally randomized (1:1), double-blind, alternative intervention–controlled, parallel-group randomized controlled trial to be conducted between October 2023 and April 2024 with a prospective follow-up for 26 weeks. This trial will evaluate whether digital interventions such as WTC improve population mental health trajectories over time. The trial will consist of 1 baseline assessment at week 0, 13 biweekly short and long follow-ups from week 24, intervention monitoring twice at weeks 6 and 26, and 1 final assessment at the end of the 26-week follow-up period. An overview of the trial process is shown in Figure 1.

The study’s overall objective is to evaluate the effectiveness and cost-effectiveness of the WTC portal by conducting a randomized controlled trial. We will use a “Knowledge-to-Action Framework” [14] with extensive stakeholder and cross-sectoral engagement and will incorporate program elements with people with lived experience.

The research questions we seek to answer with this study are the following: (1) how effective is the WTC portal in altering the trajectories of mental health and substance use, primarily anxiety, compared to usual care? (2) What is the benefit of WTC versus usual care in terms of incremental costs, health outcomes, ongoing recruitment, and maintenance costs compared to the cost per quality-adjusted life year (QALY) gained using these interventions? (3) What is the differential impact of WTC by age, sex or gender, race, and socioeconomic status?

**Figure 1 figure1:**
[figure not shown]
Flow chart showing participation stages and assessments in the Let’s Act on Mental Health Survey of 2022.

### Participants and Recruitment

Adults (N=2000) will be recruited using both paid and free web-based advertisements (social networking sites, Google advertisements, Facebook, Instagram stories, Twitter, etc). The Facebook business account of CAMH will be used to advertise the study and recruit participants. In the case of web-based advertisements, participants will click on a link in the advertisement that will direct them to a REDCap (Research Electronic Data Capture) survey, which will screen them for eligibility (see Textbox 1 for inclusion and exclusion criteria). The project’s social media pages and CAMH’s page will be used for advertisements. Further, we will also approach the participants from other ongoing studies at CAMH including the Vaping Research Panel, Smoking Panel, and those who had agreed to be contacted for future studies. We will not cold contact previous participants; we will ensure that initial contact with the participants is made by the research staff who had previously contacted and are known to them. This will help establish trust and compliance for the Let’s Act on Mental Health study.

Inclusion and exclusion criteria for the study.
**Inclusion criteria:**
Adults (≥18 years of age) residing in Canada and speaking English or FrenchAbility to complete study assessments in EnglishInterest in the use of digital interventions to improve their mental healthHaving internet access
**Exclusion criteria:**
People who are at risk for suicide (based on the 9-item Patient Health Questionnaire scores)

### Inclusion Criteria

Inclusion criteria are (1) being aged 18 years or older, (2) residing in Canada and speaking either English or French, (3) able to complete study measures in English, (4) willing or interested to use the digital interventions to improve their mental health, and (5) having internet access. Furthermore, concomitant psychotropic medication use will be allowed.

### Exclusion Criteria

The main exclusion criterion was being at risk for suicide (based on the 9-item Patient Health Questionnaire [PHQ-9] score).

Participants who are not eligible for this study after screening will be redirected to a different page, informing them that they are not eligible and thanking them for their time.

### Participant Withdrawal Criteria

Participants will not be withdrawn from the study for not wanting to receive the WTC or control intervention. Participants’ intention to use and the reason to not use the intervention will be identified through self-assessments. However, they will be withdrawn from the study if suicidal thoughts occur in any of the long-term follow-up assessments at weeks 4, 8, 12, 16, 20, and 24.

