### Sample Size

The target sample size for the population survey and learning systems sample is 2000. This sample size will also allow for the estimation of the impact of the dashboard and app recommendations on score trajectories of the PHQ-9 and 7-item Generalized Anxiety Disorder Scale (GAD-7). Based on an estimated effect size of Cohen *d*=0.17 for changes in the PHQ-9 score and Cohen *d*=0.13 for changes in the GAD-7 score (based on the expected effects of the dashboard) [15], an expected dropout rate of no more than 35% [16], and population mean and SD estimates of PHQ-9 and GAD-7 scores [17,18], we estimate having a power of 0.90 and a type I error rate of 0.05 for detecting improvements in PHQ-9 and GAD-7 scores for subsamples with at least 1000 participants. Therefore, in this study, we will have a sample size of a total 2000 participants, with 1000 randomized to each group.

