### Ethical Considerations

This study is approved by the Research Ethics Board (REB) of CAMH (reference <REB#: 037-2022>, version 7.0). The protocol will be reapproved by the REB if it requires amendment. Participants will be screened and provided a unique ID number to protect their personal information. An electronic informed consent form has been prepared in REDCap to remotely obtain consent from the participants prior to enrolling them in the trial. A REDCap survey has also been designed separately for participants’ eligibility screening at baseline, biweekly follow-ups, intervention monitoring, and final assessment over the 26-week period. Participants will be allowed to withdraw at any time without penalty.

Participants who meet the eligibility requirements of the initial screening form will be prompted to fill out a contact form with their first name and email address. Participants deemed eligible after a manual fraud check will be emailed a personalized URL to the baseline questionnaire by the research staff and those who are deemed ineligible by the fraud check will be sent a notification from REDCap about their ineligibility. The baseline questionnaire is largely composed of questions about age, sex, gender, race and ethnicity, education, and 3 digits of the participants’ postal code to later connect it with census data and community-level equity data. Lifetime history of substance use and mental health will be ascertained, including problematic alcohol use (assessed using Alcohol Use Disorders Identification Test item 3 about how often they had 6 or more drinks on 1 occasion in the past year) and drug use (assessed using the modified Drug Use Disorders Identification Test). Finally, we will measure time to completion for data quality reasons, but this variable will not be visible to participants.

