#### Secondary Outcomes

An economic analysis will be conducted by comparing incremental costs and health outcomes for the Wellbeing Tracker and WTC compared to within-person expected trajectories using a cost-effectiveness acceptability curve. These costs will be based on the costs associated with the ongoing recruitment and maintenance costs of WTC compared to the cost per QALY gained through the use of these interventions [20]. To be somewhat comparable with World Health Organization’s standards for ranking public health interventions, the determination of whether the WTC overall is highly cost-effective will be based on a threshold of CAD $124 (~US $100) per QALY gained [21]. QALYs will be estimated using the SF-6D (Short-Form Six-Dimension), calculated on the basis of the SF-12 (12-item Short Form Survey) [21]. This analysis will provide an empirical basis for the effect of allocation of health care resources in Canada. To aid other countries, we will also base cost-effectiveness calculations based on estimations that incorporate implementation costs of the Wellbeing Tracker and WTC. We will also estimate cost-effectiveness based on clinically Reliable Change Index scores (ie, 5 points on the PHQ-9 [22] and a 6-point change on the GAD-7 [23], as well as employment status. The schedule of the Let’s Act on Mental Health study is outlined in Table 1.

**Table 1 table1:** Schedule of the Let’s Act on Mental Health Survey of 2022.

Procedures	Study period (day 1 to week 26)						
Enrollment	Day 1	Week 0	Week 1	Weeks 2 and 4	Week 6	Weeks 8-24	Week 26
Eligibility screening	✓						
Informed consent	✓						
Screening assessments (PHQ-9^a^ item 9)	✓						
Drug use (DUDIT-C modified^b^)	✓						✓
Problematic alcohol use (AUDIT-C^c^)	✓						✓
Enrollment							
Demographics		✓					
3-Digit postal codes		✓					
Baseline with self-reported questionnaires (GAD-7^d^, PHQ-4^e^, Current Substance Use, SF-12^f^, and WSAS^g^)		✓					
Randomization to the WTC^h^ intervention or usual care group through an email invitation			✓				
Biweekly short and long follow-up (GAD-7, PHQ-4, Current Substance Use, SF-12, and WSAS)				✓		✓	
WTC and usual care monitoring for contamination and compliance checks					✓		✓
Final assessment (GAD-7, PHQ-4, current substance use, SF-12, and WSAS)							✓

^a^PHQ-9: 9-item Patient Health Questionnaire.

^b^DUDIT-C modified: modified Drug Use Disorders Identification Test.

^c^AUDIT-C: Alcohol Use Disorders Identification Test.

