### Statistical Analysis

A statistician who is not affiliated with this study will perform the statistical analyses for Linear random effects modeling—which accounts for repeated measures over time—that will be used to study the intervention’s effect [24]. We will also use multilevel modeling to describe within-person differences in anxiety and depression. We will then compare this observed trajectory with the control group’s trajectories.

The level of change in anxiety from weeks 0-26 (baseline to final assessment) over the 6 months’ time period is the primary trajectory of concern for mental health in this study. We will test the hypothesis that the trajectories are changing over time and the intervention’s effects are expected to be observed as changes in self-reported mood, which will be measured with the mood scores, cutoff scores, sensitivity, etc, obtained at various time points. Interactions by demographic subgroups (primarily age, gender, race, and socioeconomic status) will be assessed for identifying potential effect modifications.

Analysis will be based on the intention-to-treat principle, as this method allows to draw an unbiased conclusion regarding the effectiveness of an intervention. It also preserves the benefits of randomization, which cannot be assumed when using other methods of analysis [25]. Further, this method is also more effective in accommodating missing data, as missingness is assumed at random.

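### The suicidal-thoughts withdrawal rule conflicts with Table 1 and, when it operates, ends outcome collection before week 26 without need

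*Protocol article*

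**What the plan says.** **The rule.** Under Participant Withdrawal Criteria, people who decline the portal or the control tools stay in the study. The same section then says that "they will be withdrawn from the study if suicidal thoughts occur in any of the long-term follow-up assessments", and names weeks 4, 8, 12, 16, 20 and 24. Randomisation is at week 1, so every trigger falls after it.

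**The schedule.** Table 1 has one row naming a suicidality item, "Screening assessments (PHQ-9^a^ item 9"), ticked on Day 1 only. The later rows are "Biweekly short and long follow-up (GAD-7, PHQ-4, Current Substance Use, SF-12, and WSAS") and "Final assessment (GAD-7, PHQ-4, current substance use, SF-12, and WSAS"). Neither names the PHQ-9 or a suicidality item.

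**Other uses of the PHQ-9.** Sample Size refers to "score trajectories of the PHQ-9 and 7-item Generalized Anxiety Disorder Scale (GAD-7"), and Secondary Outcomes defines reliable change as "5 points on the PHQ-9 [22] and a 6-point change on the GAD-7 [23"].

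**The analysis.** Statistical Analysis makes change in anxiety from week 0 to week 26 the primary trajectory. It is to be fitted with a linear random-effects model by intention to treat, "as missingness is assumed at random".

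**The concern.** Two things look wrong.

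First, a safety trigger should be visible in the assessment schedule. As printed, Table 1 does not show how suicidal thoughts would be detected at the six weeks when the rule applies.

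Second, the rule ends study participation, not just use of the intervention. The section separates the two and chooses the former. No section provides for outcome data after this withdrawal; the weekly emails under Duration and Assessments concern people lost to follow-up. The people removed are selected on a state that arises after randomisation, is related to anxiety and depression, and may itself be affected by the portal.

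At stake are the later GAD-7 course, the week 26 assessment that closes the primary trajectory, and the SF-12 that feeds the QALYs, all for people whose course may be worsening. The study is fully remote and measured by questionnaire, so a safety response does not in itself require these data to stop.

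**Working it through.** **1. Schedule.** Duration and Assessments gives 14 assessments: 1 baseline + 12 biweekly (weeks 2 to 24) + 1 final (week 26) = 14, which reproduces. Post-baseline there are 13. Assessments lost after a trigger at week t = (26 − t)/2:

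| Trigger week | 4 | 8 | 12 | 16 | 20 | 24 |
|---|---|---|---|---|---|---|
| Lost, of 13 | 11 | 9 | 7 | 5 | 3 | 1 |

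Week 26 is among the losses in every column.

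**2. Rule against schedule.** The rule needs a suicidality measure at six follow-ups; Table 1 names one at screening only. Either the trigger has no scheduled measure or Table 1 is incomplete. The second is likelier, because Sample Size and Secondary Outcomes both rely on PHQ-9 change, which cannot be computed from the instruments that Table 1 lists. If so, the rule operates.

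**3. Bias in the mixed model (illustration; all inputs assumed unless stated).** The documents give no trigger rate, so 2%, 5% and 10% withdrawn in control were tried. With a GAD-7 SD of 5, the protocol's d = 0.13 is 0.13 × 5 = 0.65 points. Scores follow a random intercept and slope (ICC 0.6, slope SD 3), with the 0.65-point effect accruing linearly to week 26. The trigger depends on the current observed GAD-7 (weight 0.5), the person's own slope (weight k), a person factor (0.5) and noise (0.6), plus an arm shift in SD units. The first crossing at weeks 4 to 24 ends the data. Bias is the random-slope estimate minus the same fit to full data; positive means benefit understated. Each cell used 10 runs of 100,000 per arm, with Monte Carlo SE at most 0.002. Other dropout is not modelled.

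| Arm shift in suicidality (SD) | k = 0.3: 2 / 5 / 10% | k = 0.6: 2 / 5 / 10% |
|---|---|---|
| 0 | 0.0018 / 0.0033 / 0.0039 | 0.0018 / 0.0047 / 0.0070 |
| −0.13 (portal lowers) | 0.0100 / 0.0199 / 0.0320 | 0.0157 / 0.0340 / 0.0539 |
| −0.17 | 0.0119 / 0.0245 / 0.0399 | 0.0192 / 0.0412 / 0.0663 |
| +0.13 (portal raises) | −0.0092 / −0.0178 / −0.0291 | −0.0158 / −0.0308 / −0.0477 |
| +0.17 | −0.0131 / −0.0258 / −0.0405 | −0.0222 / −0.0429 / −0.0665 |

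With k = 0 the absolute bias is at most 0.0016 for every shift, which is zero within simulation error.

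- No arm shift: 0.0018/0.65 = 0.3% to 0.0070/0.65 = 1.1% of the effect.
- Arm shift and k > 0: from 0.0092/0.65 = 1.4% to 0.0665/0.65 = 10%, in either direction.

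**4. A second illustration.** With a true effect of −0.20 SD and about 2% to 21% withdrawn, depending on the observed or the underlying anxiety level, the mixed model gave −0.197 to −0.201. The week 26 comparison restricted to completers shrank to between −0.197 and −0.179.

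**5. Scale.** With 35% dropout, 1000 × 0.65 = 650 remain per arm, and SE = 5 × √(2/650) = 0.277. The largest case is 0.067/0.277 = 0.24 of a standard error.

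**The case against.** **The schedule gap may be condensation.** This is a journal article, and Table 1 merges short and long follow-ups into one row. The full protocol may list the PHQ-9 at the long ones. That is probably right, and it is why a reader should not infer that the trigger has no measure at all. The article nevertheless contradicts itself: the row does list its instruments, and it names the PHQ-4.

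**The rule is a clinical and ethical choice.** It mirrors the entry exclusion, and the ethics board approved the study. The board's authority over the safety response stands. It does not follow that outcome collection must end: referral and a voluntary questionnaire can coexist, and whether that is acceptable is a question to put to the board.

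**Material bias is not shown.** This stands. A reader might infer serious bias in the primary result, or that any difference in event rates favours the arm with more events. The k = 0 runs contradict the second inference: differing rates alone gave no bias. The 10% figure needs 10% withdrawn in control, the stronger dependence on the unobserved slope and a 0.17 SD effect on suicidality, all in people already screened on item 9.

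**A reader might also set the bias against a standard error taken from the stated 90% power:** 0.65/(1.960 + 1.282) = 0.20, so 0.067/0.20 is about one third. That power is not reached by a two-sided two-group test with 650 per arm, where it is 0.649 at d = 0.13. The ratio of 0.24 is the safer one.

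**Conclusion.** The point holds, with minor to moderate importance. The withdrawal rule and Table 1 conflict, most likely because Table 1 is incomplete. When the rule operates, it loses 11, 9, 7, 5, 3 or 1 of the 13 post-baseline assessments and always week 26. These counts follow from the document alone.

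A reader might call this a breach of intention to treat. It is not: participants can still be analysed as randomised, and their scores before withdrawal stay in the model. It is incomplete follow-up imposed by the protocol and avoidable.

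The missing-at-random assumption is adequate, or nearly so, if the trigger depends on the person's course only through recorded scores, and doubtful otherwise. Appreciable bias needs both dependence on the unobserved course and event rates that differ by arm. In that case the benefit is understated if the portal reduces suicidal thoughts and overstated if it increases them. The actual size is unknown, because the document gives no trigger rate; every bias figure here rests on assumed inputs.

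**What to change.** (a) In Table 1, schedule PHQ-9 item 9 at weeks 4, 8, 12, 16, 20 and 24.

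(b) Replace withdrawal from the study with a safety response whose content the clinical team and the ethics board agree. Continue GAD-7, SF-12 and the other remote questionnaires to week 26 for those willing.

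(c) Report the number of these events by arm.

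**Cost.** One table row, a count by arm, some contact for the safety response, and an ethics amendment, for which Ethical Considerations already provides: "The protocol will be reapproved by the REB if it requires amendment". The change cannot recover data already lost in the first wave, which Results reports as fully collected. How many participants would come under the amended rule cannot be stated, because the documents do not say whether the 453 respondents count toward the target of 2000.
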